#### 493 **CONCOMITANT MEDICATIONS**

##### 494 **Permitted concomitant medications**

495 Concomitant treatment will be permitted unless its use is contraindicated or there are  
496 significant interactions with NicaPlant®.

##### 497 **Non-permitted concomitant medications unless indicated**

498 NicaPlant® is contraindicated in those who are hypersensitive to any component of a  
499 nicardipine-containing product.

500 A list of non-permitted concomitant medications will be provided to sites based on available  
501 information on the known interaction with nicardipine.

502

| Drug class: | Specific active substance
(if applicable) | Effect on Nicardipine: |
|-------------|----------------------------------------------|------------------------|
|             |                                              |                        |

|                        |                                                                                          |                                                                                |
|------------------------|------------------------------------------------------------------------------------------|--------------------------------------------------------------------------------|
| CYP450 3A4 Inducers    | Carbamazepine
Rifampicin                                                              | Alter the plasma levels of
nicardipine.                                     |
| CYP450 3A4 Inhibitors  | Cimetidine
Grapefruit Juice                                                           | Alter the plasma levels of
nicardipine.                                     |
|                        | Cyclosporine
Tacrolimus
Sirolimus                                                  | Elevated levels of
cyclosporine, tacrolimus or
sirolimus in the plasma.  |
| Calcium Ion Antagonist | Cardene®                                                                                 | Careful monitoring of serum
digoxin levels as levels
could be increased. |
| Beta-Blocker           | Fentanyl Anaesthesia with
concomitant use of Beta-
Blocker and Calcium
Blockade | Severe Hypotension                                                             |
| Anti-Hypertensives     |                                                                                          | Postural Hypotension                                                           |

503

504

## 505 TREATMENT(S)

### 506 Appearance and content

#### 507 *Investigational Medicinal Product*

508 NicaPlant® is a nicardipine modified release formulation, it is presented in the form of a rod-  
509 shaped implant (2 mm x 10 mm, 4 mg nicardipine load).

510 NicaPlant® will be given on top of the standard of care-treatment as determined at the sites  
511 according to the treatment guidelines. [8]

512 A main difference to the previous study is the lack of limitations for an additional treatment  
513 with Nimodipine or any other treatment needed according the treatment guidelines since the  
514 safety of patient should not be reduced. Furthermore, the sovereignty of the study sites will  
515 not be subducted by the study since patients in emergency situations within the intensive care  
516 unit need an individual therapy adapted to their needs and with no delays.

### 517 Dosage and administration

#### 518 *Dosage*

519 NicaPlant® will be administered as per the implantation protocol. The selected dose is 10  
520 implants/ patient.

521

#### 522 *Administration*

523 Following aneurysm clip ligation, the NicaPlant® implants will be placed into the basal  
524 cisterns, in direct contact with the exposed cerebral blood vessel walls.

525 The distribution of the implanted polymers will follow a pre-defined protocol dependent on  
526 aneurysm location to achieve maximum delivery of nicardipine to the vessel segments at  
527 highest risk of vasospasm.

528

Example Implantation Sites:

Anterior communicating artery aneurysm (A)

Middle cerebral artery aneurysms (B)

Internal carotid artery aneurysms(C):

[figure not shown]

529 Sites of NicaPlant® placement are defined in the Implantation Protocol for all sites of saccular  
530 aneurysms.

531 **Packaging**

532 IMP is assembled for Qualified Person Certification and release for use in the clinical trial at  
533 the manufacturing company AMW GmbH, [name] and  
534 delivered as 10 implants in lid covered boxes, placed into a pouch terminally gamma  
535 sterilised.

536 **Labelling**

537 All study medications will be labelled in accordance with Annex 13: Manufacture of  
538 investigational products and local requirements.

539 As a centralised randomisation system is used, the randomisation number of the patient will  
540 not be pre-printed on the label. After a patient is randomised to the Standard of care plus  
541 NicaPlant® group and received a randomisation code through the IWRS system, the code will  
542 be written onto the label of the used implant box by the site's study team.

---

 Drawings from Barth M, Capelle HH, Weidauer S, et al., Effect of nicardipine prolonged-release implants on cerebral vasospasm and clinical outcome after severe aneurysmal subarachnoid haemorrhage: a prospective, randomised, double-blind phase IIa study, Stroke, 2007;38:330–6.

543 If there is an issue during implantation, like one or more dropped implants, a second implant  
544 box will be used for the patient and the randomisation code will be also written onto the label  
545 of the second implant box.

546

547

## 548 **Blinding and randomisation**

### 549 ***Randomisation***

550 Up to 40 patients (20 will receive standard of care, 20 will receive standard of care and 10  
551 NicaPlant® implants) will be included in the study.

552 Patients that withdraw prior to hospital dismissal will be replaced. Replacement patients will  
553 receive the same treatment as the withdrawn patient. A maximum of 10 replacements will be  
554 done. Patients who die will be considered to have completed the study and will not be  
555 replaced.

556 Patients are to be randomised at Visit 1 within 48 hrs of aneurysm rupture. A member of the  
557 study team will randomize patients in the IWRS system and will receive a randomisation  
558 code assigned to the patient. It is essential for all patients that a participation within the study  
559 is not causing any delay in the treatment and the safety and wellbeing of the patients needs to  
560 be the main focus all the time.

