### 375 ***Blinding***

376 The study design does not include a placebo implant for ethical reasons; therefore, it is not  
377 possible to blind the neurosurgeons performing the aneurysmal clipping procedure to study  
378 treatment. Accordingly, the standard of care control group will receive no intracranial  
379 treatment (i.e., no placebo implants).

380 Patient selection bias is controlled by randomisation; patients will be blinded to which  
381 treatment they are receiving (implant or standard of care group) throughout the study i.e. the  
382 study is single blinded.

383 Therefore, the treatment groups are as follows:

- 384 • Patients receiving standard of care and NicaPlant® implants.

385 OR

- 386 • Patients in standard of care.

387 Patients will be assigned a corresponding randomisation code at consent; in the operation  
388 room, following aneurysm clip ligation, a member of the unblinded operation room team will  
389 verify the randomisation code using the IWRS system; if the patient is to receive NicaPlant®  
390 implants the implantation procedure goes ahead; if not, no implantation is carried out.

391 In emergency situations, when the identity of the treatment arm must be made known, the  
392 treatment arm of the patient will be available to designated and authorised personnel using  
393 the IWRS system. Access to the IWRS is held by the responsible neurosurgeon and other

designated authorised site personnel, to be agreed prior to study commencement. Full details of the randomisation including user access will be provided in the study IWRS user guide.

Study team staff (including those undertaking Safety Assessments, TCD readings, mGCS assessments and Clinical Outcome assessments) will be blinded to the treatment. An independent specialist, also blinded to the treatment, will undertake the analysis of the angiograms and computed tomography imaging of the brain for the diagnosis of cerebral vasospasm and new cerebral infarcts, respectively, for study endpoint assessment.

Trained personnel collecting data on clinical outcome at week 12 and 52 will also be blinded. In cases of DIND or anti-vasospasm rescue therapy as determined by the sites, all required data (e.g. clinical data, case narratives, angiograms, CTs) will be provided to a board of blinded independent experts to adjudicate on the presence of DIND or anti-vasospasm rescue therapy.

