#### **Exclusion criteria**

1. SAH due to other causes (e.g. trauma, fusiform or mycotic aneurysm).
2. World Federation of Neurosurgery (WFNS) grade I, II and V patients.
3. Pregnant or Lactating Women.
4. Intraventricular or intracerebral blood, in the absence of subarachnoid blood.
5. Treatment of aneurysm via endovascular embolisation.
6. Presence of moderate or severe vasospasm on screening angiography.
7. Any known or CT /MRI evidence of previous major cerebral damage
8. Evidence of a cerebral infarction with neurological deficit on pre-treatment CT/MRI.
9. History of malignant disease (except for non-melanoma skin cancer) within the previous 5 years or any history of malignant brain tumours or brain metastasis.
10. Patients who have received an investigational product or participated in another interventional clinical study within 30 days prior to randomisation.
11. Patients with known allergy for Poly(D,L-lactide-co-glycolide) (PLGA) or nicardipine.
12. Major complication during aneurysm repair such as, but not limited to, massive intraoperative haemorrhage, brain swelling, or inability to secure the ruptured aneurysm.

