#### **Subject withdrawals**

In all circumstances, patients and/or personal legal representatives should be made aware of the rights to refuse participation in a clinical trial and are entitled to freely withdraw their informed consent, without giving reasons. Patients and/or personal legal representatives should be assured that the withdrawal from the trial will not cause prejudice, will not result in any determinant and will not affect treatment. In addition, refusal to give consent or withdrawal of consent to participate in research must not lead to any liability or discrimination (e.g., with regard to insurance or employment) against the person concerned.

The Investigator also has the right to withdraw subjects from the study in the event of:

- Use of any concomitant medication specified as not permitted
- Noncompliance with the protocol and/or lack of willingness or commitment to co-operate in all phases of the study
- Protocol deviations
- Pregnancy after entry into study
- Adverse event which is considered intolerable by the patient and/or legal representative

471 • Intercurrent illness that necessitates pharmacological treatment with a drug which  
472 interacts in any way with the test treatment

473 • Development of an exclusion criterion

474 Should a patient and/or personal legal representative decide to withdraw for other reasons, all  
475 efforts will be made to complete and report the observations as thoroughly as possible. A  
476 complete final evaluation at the time of withdrawal will be performed with an explanation of  
477 the exact reason why the subject is withdrawing from the study.

478 The Investigator is responsible for the optimal individual treatment of the patient.

479 The Investigator must fill in the “Study termination” in the case reporting form (CRF)  
480 explaining all reasons for withdrawal.

481 After a patient withdraws from the trial, the Investigator is still responsible for reporting  
482 SAEs considered causally related to the study drug as well as any pregnancy and outcome of  
483 the pregnancy. In addition, the Investigator needs to ensure appropriate treatment and follow-  
484 up of each adverse event still ongoing at the time of the patient’s discontinuation.

485 No reproductive toxicology or embryo/foetal development studies have been performed with  
486 NicaPlant®. The product will not be used in pregnant women.

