### 590 **Continuous Assessment**

591 The following assessments will be carried out on a continuous basis and as events arise:

592 Adverse Events and separately, bacterial meningitis and shunt-dependent hydrocephalus.

593

594 **Visit 1: Pre-implantation assessment (within 48 hours of aneurysm rupture and SAH)**

595 The following assessments will be performed and documented in all patients admitted with a  
596 diagnosis of spontaneous aneurysmal SAH and consented appropriately to the study:

- 597 • Inclusion/Exclusion Criteria (screening failures to be recorded)
- 598 • Angiography (DSA) of the ICA bilateral and both vertebral arteries
- 599 • CT of the brain
- 600 • Demographics/Medical History
- 601 • Physical examination
- 602 • Pregnancy test
- 603 • Vital signs (blood pressure, pulse rate, respiratory rate, temperature)
- 604 • ECG
- 605 • Haematology, serum biochemistry
- 606 • mGCS
- 607 • Randomisation
- 608 • Informed consent procedure according to section 14

609  
610 The assessments for the participation in the study shall not cause any delay in the  
611 treatment of the patients. The safety and wellbeing of the patients needs to be the main  
612 focus all the time.

613  
614 **Visit 2: Clip Ligation & Implantation (within 72 hours of aneurysm rupture)**

615 Eligible patients will be randomised to either NicaPlant® implantation or no implantation.

- 616 • Clip ligation
- 617 • Implantation (if randomised to the study group) of NicaPlant® implants
- 618 • PK Plasma sampling (0, 6, 12, 24 hrs after implant,  $\pm 20$  minutes each)
- 619 • CSF sampling (patients with EVD and CSF sampling performed for standard of care  
620 only)
- 621 • CT brain scan, post-surgery,  $36 \pm 12$  hours from clip ligation (on NicaPlant®  
622 application) to identify surgery related ischemic lesions and for baseline assessment.

623  
624 **Ongoing Assessments (day of surgery to day of patient discharge or day 21 $\pm$ 1 post**  
625 **aneurysm, whichever occurs first)**

626  
627       • Daily – mGCS, TCD reading for evidence of vasospasm (to be confirmed by DSA),  
628       CSF sampling (patients with EVD in days when CSF sampling is performed for  
629       medical reasons only), PK Plasma sampling on days blood is drawn for medical  
630       reasons but only once per day (time of sampling to be recorded).

631  
632 **Visit 3: Angiography (DSA) (day 8±1 post aneurysm rupture or whenever vasospasm is**  

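### Randomisation is set before surgery, but exclusion criterion 12 can be judged only during surgery, and nothing requires it to be recorded before the arm is read

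*Protocol*

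**What the plan says.** **Time of randomisation.** The Randomisation text under Treatment(s), Blinding and randomisation, says: "Patients are to be randomised at Visit 1 within 48 hrs of aneurysm rupture". The Blinding text under Study Design agrees: "Patients will be assigned a corresponding randomisation code at consent". The Visit 1 list in the Study Plan also includes randomisation. Against these, the opening sentence of Visit 2 (clip ligation and implantation, within 72 hours of rupture) reads "Eligible patients will be randomised to either" implantation or no implantation.

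**The criterion.** Exclusion criterion 12 is: "Major complication during aneurysm repair such as, but not limited to, massive intraoperative haemorrhage, brain swelling, or inability to secure the ruptured aneurysm".

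**Reading the arm.** The Blinding text places the check of the code in the operating room ("room, following aneurysm clip ligation, a member of the unblinded operation room team will" verify it in the IWRS, the web-based randomisation system). The table of blinded and unblinded personnel lists the implantation operating team as unblinded.

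**After randomisation.** Subject withdrawals gives the investigator the right to withdraw a subject for, among other reasons, "Development of an exclusion criterion". Replacement of Withdrawn Patients says that those who withdraw before discharge or day 21 are replaced, that the replacement receives the same treatment, and that at most 10 replacements are made. Patients who die are not replaced. The protocol does not say how a randomised patient who meets criterion 12 is to be handled.

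**The concern.** An exclusion criterion should be settled before allocation. Here one criterion describes an event of the operation itself, and allocation precedes the operation. Exclusion under it is therefore always exclusion after randomisation.

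Two things are at stake. First, patients with a complicated repair are plausibly at higher risk of poor outcome. If they leave and are replaced, the patients compared are no longer those whom chance assigned, because the replacement's arm is fixed by the arm of the patient who left. Second, the criterion is a judgement, since its examples are expressly not exhaustive. If it is made, or revised, by an unblinded team after the arm is known, a difficult operation could be excluded in one arm and kept in the other.

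The conflict over the visit adds to this. A site following the Visit 2 sentence and a site following the Visit 1 list would randomise different sets of patients.

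**Working it through.** **1. Order of events**

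| Step | When | Source |
|---|---|---|
| Consent, code assigned, randomisation | Visit 1, within 48 h | Study Design, Blinding; Treatment(s), Randomisation; Visit 1 list |
| Criterion 12 can first arise | Visit 2, during repair, within 72 h | Exclusion criteria; Visit 2 |
| Arm read by operating team member | Visit 2, after clip ligation | Study Design, Blinding |
| Withdrawal possible | Any time after entry | Subject withdrawals |
| Replacement, same arm | If withdrawn before discharge or day 21 | Replacement of Withdrawn Patients |

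The second row always follows the first, so no patient can fail criterion 12 before randomisation. No entry in the protocol fixes the order of judging criterion 12 and reading the arm. The replacement allowance is 10/40 = 25% of the planned sample.

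**2. The plan's own figure**

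Inputs from Power & Sample size: 20 per arm, vasospasm 20% (active) against 70% (control), Fisher's exact test, two-sided 5%. Exact power is the sum, over all 21 × 21 outcomes (x, y), of Bin(x; 20, 0.20) × Bin(y; 20, 0.70) wherever the Fisher p-value is at most 0.05. Result: 84.6%, against 84% stated. The figure reproduces, and the sample size is not in question.

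**3. Sensitivity to a few cases**

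The number of criterion 12 events is an assumption throughout, because the documents give none.

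(a) *Excluded and not replaced, equally in both arms* (same formula, smaller n):

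| Per arm | 20 | 18 | 17 | 16 | 15 |
|---|---|---|---|---|---|
| Power | 84.6% | 83.5% | 79.2% | 74.0% | 68.0% |

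(b) *Kept as randomised, with k of the 20 implant-arm patients not implanted and at the control rate of 70%.* The mean active-arm rate is [(20 − k) × 0.20 + k × 0.70]/20. For k = 2 this is (3.6 + 1.4)/20 = 25%. For power, the active count is the sum of Bin(20 − k, 0.20) and Bin(k, 0.70).

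| k | 0 | 1 | 2 | 3 | 4 |
|---|---|---|---|---|---|
| Mean active rate | 20% | 22.5% | 25% | 27.5% | 30% |
| Power | 84.6% | 79.5% | 73.6% | 67.0% | 60.1% |

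(c) *Worst-case illustration of arm-dependent exclusion.* There is no true effect, and up to k patients who would have had vasospasm are removed from the active arm only, without replacement. Two-sided type I error:

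| k | 0 | 2 | 3 | 4 |
|---|---|---|---|---|
| 50% event rate in both arms | 2.0% | 5.2% | 8.1% | 11.9% |
| 70% event rate in both arms | 2.5% | 4.1% | 5.3% | 6.5% |

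Case (c) differs from the plan, which replaces withdrawn patients in the same arm. It shows direction and scale only.

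**4. After the change**

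If allocation follows clipping and the recording of criterion 12, every randomised patient has passed the criterion. The calculation in step 2 applies unchanged: 20 per arm, 84.6%.

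**The case against.** The strongest reply is that the protocol already delays the reading of the arm. Only a code is assigned at consent, and the check comes after clip ligation. Massive haemorrhage or failure to secure the aneurysm would normally show before that step, with the arm still unread. This stands, and it is the main safeguard. It does not cover complications judged after the check, such as swelling, and it is not tied to any record of the criterion.

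Several stronger readings are tempting but not supported:

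- *The surgeon knows the arm before operating.* The neurosurgeon's IWRS access is described directly after the sentence on emergency unblinding. The protocol does not show routine access before clipping, although it does not expressly exclude it.
- *Every patient meeting criterion 12 is withdrawn and replaced.* Withdrawal is a right of the investigator and not a duty, and deaths are not replaced. Membership of the full analysis set may be defined in the SAP, which is not at hand. It is therefore not established that the analysed groups will differ from the randomised ones.
- *Visit 2 is the protocol's rule for randomisation.* The Visit 1 list in the same section contains randomisation and the Visit 2 list does not. The Visit 2 sentence is the outlier.
- *A switch to endovascular treatment (criterion 5) is the same problem.* It occurs before the arm is due to be read, so it can cost a place but gives little route to arm-dependent exclusion.
- *A rate such as 10–15% (4–6 of 40 patients) measures the bias.* It has no source in the documents, and it would count exclusions in both arms, not the difference between arms.

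**Conclusion.** The point holds as a defect in the order of steps. Criterion 12 is open-ended and can be met only after randomisation. A patient who meets it may be withdrawn and replaced in the same arm, and nothing requires the judgement to be on record before an unblinded team reads the arm. The Visit 1 and Visit 2 statements on randomisation also conflict and must be reconciled.

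The size is unknown, since the frequency of criterion 12 events is not given. The scenarios show only that a trial of 40 is sensitive. Three losses per arm without replacement take power below 80%, and so does a single unimplanted implant-arm patient kept in the analysis at the 70% control rate. Selective removal of two to four patients could raise the type I error above 5% under worst-case assumptions. An analysis-set definition alone cannot resolve this: excluding these patients risks bias, and keeping them dilutes the effect. It should be fixed, but because the arm is meant to be read only after clipping, it falls short of invalidating the design.

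**What to change.** Keep consent and screening at Visit 1. Make the existing post-clipping IWRS query the randomisation step, and have the system give the allocation only after criterion 12 has been entered as met or not met. Patients who meet it, or who are not clipped, are then screen failures, neither randomised nor replaced. State that criterion 12 cannot be used to withdraw a patient once the allocation has been given. This concerns study membership only and leaves clinical decisions in the operating room untouched.

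Amend the Blinding text under Study Design, the Randomisation text under Treatment(s), and the randomisation item in the Visit 1 list to match. The Visit 2 sentence then fits.

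The cost is a protocol and IWRS amendment, and an implant box at hand for every case. The operating team already queries the system at this point, so no new step is added in theatre beyond the criterion 12 entry. The sample size stays at 20 per arm.
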